## Abstract

**Background:**

Chronic lower limb ischemia develops earlier and more frequently in patients with type 2 diabetes mellitus. Diabetes remains the main cause of lower-extremity non-traumatic amputations. Current medical treatment, based on antiplatelet therapy and statins, has demonstrated deficient improvement of the disease. In recent years, research has shown that it is possible to improve tissue perfusion through therapeutic angiogenesis. Both in animal models and humans, it has been shown that cell therapy can induce therapeutic angiogenesis, making mesenchymal stromal cell-based therapy one of the most promising therapeutic alternatives. The aim of this study is to evaluate the feasibility, safety, and efficacy of cell therapy based on mesenchymal stromal cells derived from adipose tissue intramuscular administration to patients with type 2 diabetes mellitus with critical limb ischemia and without possibility of revascularization.

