### Recruitment of eligible participants

Patients will be recruited by the attending clinicians (vascular surgeons) among the population of chronic, type 2 DM patients with peripheral arteriopathy that is usually under periodic follow-up in the outpatient clinic. Proposal to participate in the clinical trial will take place in one of these routine outpatient visits. Clinicians will explain to each subject the nature of the study, its purposes, procedures, expected duration, and the potential risks and benefits related to participation in the trial, as well as any inconvenience that this may entail. Patients will have enough time to read and understand the explanations before dating and signing the informed consent and will receive a copy of the signed document. Eligible patients will be (1) those aged between 40 and 90 years; (2) with type 2 DM diagnosed for more than one year; (3) with severe vascular arteriosclerosis, defined as Rutherford-Becker (RB) category 4 and 5 [23], mono or bilateral; and (4) with impossibility of surgical or endovascular revascularization or failure of revascularization surgery performed, at least 30 days before inclusion in the study. Patients with CLI and tissue loss in the target limb (RB category 6) or previous major amputation in the target limb will be excluded from the trial. Detailed eligibility criteria are described in ClinicalTrials.gov (NCT04466007). During trial conduct, periodic contacts with investigators and a trial newsletter are foreseen to assess possible difficulties in recruitment in advance and to keep investigator team informed of recruitment evolution. No specific methods to minimize attrition are foreseen. Eligible patients are severely ill patients that are usually adherent to medical visits, and thus a high drop-out rate is not expected.

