Regarding the allogeneic treatment presented in this protocol and possible risk of immune rejection, MSC are considered to have an immunoprivileged status. These cells display a low expression of MHC-HLA class I and are constitutively negative for HLA class II [28], thus avoiding the presentation of antigens to cytolytic T lymphocytes and immunological rejection. Furthermore, an autologous use would entail MSC isolation from multipathological patients. It has been suggested that the hyperglycemic environment and metabolic disorders associated with diabetes affect the biological properties and angiogenic capacity of cells [29–31]. Ad-MSC isolated from young healthy donors are more likely to present uniform cellular properties [7]. Treatment will be administered intramuscularly at the infrapopliteal level, at 25 points in the ischemic area parallel to the vascularization of the affected limb (Fig. 4). Treatment administration will be performed in the operating room, after patients have gone through mandatory presurgical assessment. As the IMP consists of a living drug, the importance of standardizing handling of Ad-MSCs was emphasized during the design of the clinical trial. Hence, a protocol for the management and administration of the medication was established. Doses are proposed according to previous experience of the group and bibliographical data. In previous trials (Phase I/IIa), 1 × 10^6^ cells/kg of patient weight have been used [7, 22, 32]. In parallel and considering the results of these tests, as well as the safety demonstrated in the administration of Ad-MSC, it seems justified to check whether a higher cell dose could improve the results obtained to date. In case of bilateral affection, the limb to be treated will be the more damaged one. In addition to the IMP administration and study procedures, patients will be managed according to routine clinical practice. Patients may voluntarily discontinue the study and will be withdrawn from the study if they present any clinically relevant condition that may represent a risk. After the end of the trial, patients will be managed according to best clinical practice.

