#### Secondary outcome measures

Efficacy will be assessed through the following variables:

(a) Vascularity in the target limb will be assessed through mean change in percentage of vascular flow measured by MRI in the target limb at 12 months from baseline between groups. MRI will be centrally read by a blinded radiologist. (b) Disease severity will be evaluated through percentage of patients with an improvement in RB category at 3, 6, and 12 months from baseline [33] between groups. This scale is usually used in patients with chronic arterial disease to classify chronic arterial disease into clinical categories (category 0, asymptomatic; category 1, mild claudication; category 2, moderate claudication; category 3, severe claudication; category 4, pain at rest; category 5, minor tissue loss; category 6, ulcer o gangrene). (c) Ulcer healing (if any) will be assessed through the percentage of patients with a decrease in SVS-“WIfI” wound classification [34, 35] at 3, 6, and 12 months from baseline between groups. SVS-WIfI classification aims to be as functional in diagnosing PAD as the tumor-node-metastasis-based diagnosis system (TNM). Three measurable parameters are collected: wound (extension and depth), ischemia (blood flow), and foot infection (presence and extension). (d) PAD evolution will be evaluated by % of patients with an increase in ankle-brachial index at 3, 6, and 12 months from baseline between groups [36]. (e) Pain intensity will be assessed through mean change in visual analogue scale (VAS) from 0 to 10 cm, as described by the patient (0, absence of pain; 1–3, mild; 4–7, moderate; 8–10, severe) and percentage of patients with an improvement in pain intensity at rest at 3, 6, and 12 months from baseline between groups. (f) Percentage of patients with a decrease in temperature (°C), increase in gastrocnemius muscle perimeter (cm) and decrease in neuropathic symptoms of the treated limb compared with contralateral at 3, 6, and 12 months from baseline. (g) Mean change in percentage of amputations in each group at the end of the study will be registered.

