#### Statistical analysis

Primary, secondary, and tertiary outcomes (safety, efficacy, and quality of life) will be assessed in intention to treat (ITT) and per protocol (PP) populations [39]. ITT population will include all patients who sign the informed consent and receive the investigational product. PP population will include patients who complete the 12-month follow-up period. A descriptive analysis of baseline characteristics of patients included in three groups will be performed. Quantitative variables will be expressed as mean and/or median and standard deviation and/or range. Qualitative variables will be expressed as percentages. When possible, the 95% confidence interval of each of the estimates made will be calculated. To analyze the primary outcomes, 24 h and 3, 6, and 12 months complication rates will be described and compared for the three groups using the Chi-square test or, if necessary, the Fisher exact test. The analyses of the secondary and tertiary outcomes will be performed as follows: qualitative variables will be described in terms of the percentage of improvement of the medical condition in each group and compared using the Chi-square test, or alternatively Fisher’s exact test. VAS scale, SF-12 scale, VascuQuol-6 scale, and the rest of the quantitative variables will be assessed by describing changes in variables at 3, 6, and 12 months from baseline, in an absolute and relative way. Changes at 3, 6, and 12 months in the three groups will be described and compared using the analysis of variance test, or the Kruskal-Wallis test, depending on whether or not the data follow a normal distribution. In all comparisons, a global comparison of the three groups and comparisons between groups by pairing will be carried out (low-dose treatment versus placebo, high-dose treatment versus placebo, high-dose treatment versus low dose, both treatment groups versus placebo). P values will be corrected by Bonferroni test. Regarding handling of missing data, a complete case analysis will be performed if percent of missing data is less than 5%. In another case, a data imputation will be performed for those variables with 25% or less missing values. Variables with more than 25% missing values will be removed from the analysis. The statistical analysis will be carried out by the statistical service of the Jiménez Díaz Foundation University Hospital. Data analyst will be blinded.

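### Secondary outcome (f) counts a fall in treated-limb temperature as an efficacy response, against the trial's perfusion rationale; its contralateral reference is a lesser fault in bilateral disease

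*Protocol article*

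**What the plan says.** The protocol article's section on secondary outcome measures opens with "Efficacy will be assessed through the following variables". Item (f) is a responder percentage with three components. The first two are "Percentage of patients with a decrease in temperature (°C), increase in gastrocnemius muscle perimeter (cm"); the third is "decrease in neuropathic symptoms of the treated limb compared with contralateral at 3, 6, and 12 months from baseline".

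Under Statistical analysis, "qualitative variables will be described in terms of the percentage of improvement of the medical condition in each group" and compared by chi-square or Fisher's exact test. The same section also plans to describe changes from baseline in quantitative variables and compare them by analysis of variance or Kruskal-Wallis.

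On the aim of treatment, the abstract says that "it is possible to improve tissue perfusion through therapeutic angiogenesis". Item (a) measures vascular flow in the target limb by MRI, and item (d) counts patients whose ankle-brachial index rises.

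On laterality, eligible disease is "defined as Rutherford-Becker (RB) category 4 and 5 [23], mono or bilateral". The Interventions section adds: "In case of bilateral affection, the limb to be treated will be the more damaged one".

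**The concern.** Item (f) puts a fall in temperature beside two changes that are plainly favourable, a larger calf and fewer neuropathic symptoms. The analysis section then reports such variables as percentage improved. On that text, a cooler treated limb is a success. The treatment is supposed to bring more blood to an ischaemic limb, which one would expect to warm it, and the other perfusion outcomes are scored in that direction. A product that worked as intended would then look worse than placebo on this component.

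A second, smaller matter is the reference limb. In a patient with bilateral disease the other leg is ischaemic too and may change during the year. No alternative reference is given for these patients, and randomisation is not stratified, so their share is not balanced between arms by design.

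**Working it through.** **Is there a figure to reproduce?** No. The article gives no effect size, standard deviation or expected rate for item (f), and states that no formal sample size calculation was made. Everything numerical below is illustration on assumed values.

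**Step 1: what direction does the text set?**
- Item (f) is headed as efficacy and counts a decrease in temperature.
- The analysis section treats the counted direction as improvement.
- The rationale is better perfusion; items (a) and (d) look for more flow and a higher index.
- No section says why a cooler limb would be better.
- Could the phrase mean that the temperature gap between the limbs narrows? The same closing words, "of the treated limb compared with contralateral at 3, 6, and 12 months from baseline", also govern the increase in perimeter. Read as a gap, that component would reward growing asymmetry between the calves. The gap reading does not fit.

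**Step 2: size of the reversal, treated limb alone.** Assume that the change in temperature is normal with SD 1, has mean 0 on placebo and mean *d* on active treatment. Then P(decrease) = Φ(0) = 50% on placebo and Φ(−*d*) on active.

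| Assumed warming *d* (SD) | Decrease, active | Decrease, placebo | Active minus placebo | Increase, active |
|---|---|---|---|---|
| 0.25 | 40.1% | 50% | −9.9 points | 59.9% |
| 0.5 | 30.9% | 50% | −19.1 points | 69.1% |
| 0.8 | 21.2% | 50% | −28.8 points | 78.8% |

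Counting an increase instead gives the same difference in favour of active treatment. With 30 per arm, the power of a two-proportion comparison to declare the wrong-way difference significant at 0.05 is about 12%, 32% and 65% across the three rows.

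**Step 3: size if taken as treated minus contralateral.** The SD of the difference is √(2(1−ρ)), where ρ is the correlation between the limbs' changes. With ρ = 0 it is √2, so P(decrease) on active is Φ(−*d*/√2):
- *d* = 0.25: Φ(−0.177) = 43.0%, a difference of −7.0 points.
- *d* = 0.5: Φ(−0.354) = 36.2%, a difference of −13.8 points.
- *d* = 0.8: Φ(−0.566) = 28.6%, a difference of −21.4 points.

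The reversal is smaller than in Step 2. At ρ = 0.5 the SD is 1 and the Step 2 figures return.

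**Step 4: what does a diseased reference limb do?** Keep *d* = 0.5 and ρ = 0, and let the other limb cool by an assumed 0.5 SD in bilateral patients, equally in all arms. A simulation with 1,000,000 draws per cell gave:

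| Bilateral share | Relative decrease, placebo | Relative decrease, active | Difference |
|---|---|---|---|
| 0% | 50% | 36.2% | −13.8 points |
| 50% | 43.0% | 30.1% | −13.0 points |
| 100% | 36.1% | 24.1% | −12.1 points |

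The differences were taken before rounding. The sign and approximate size of the arm difference hold. What moves is the percentage within each arm: on placebo it drops from 50% to 36% with no change at all in the treated limb.

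**The case against.** **The continuous analysis is already there.** Temperature in °C and perimeter in cm are quantitative, and the Statistical analysis section provides for comparing change from baseline between groups. In that analysis a warming effect would carry its proper sign. This stands, and it makes the remedy easier. It does not remove the error, because the outcome as defined is the responder percentage, and nothing says which analysis takes precedence.

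**A decrease may be intended.** The Background credits these cells with anti-inflammatory properties, and the Discussion describes a greater inflammatory response in these patients. A fall in temperature could be meant as less inflammation. No section says so for this outcome. That better perfusion warms a limb is likewise general physiology and not a statement in the article. The sponsor should therefore be free to justify a decrease if that was the intention.

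**Stronger readings that the article does not support.**
- A reader might infer that the contralateral reference also turns the result round. It does not: under randomisation, change in the untreated leg is expected equally in all arms, and Step 4 shows the difference barely moving.
- A reader might infer that worsening of the other leg always passes for improvement of the treated one. For temperature as written it works the other way: a cooling reference makes the treated limb relatively warmer, so fewer patients count. The inference fits only perimeter and neuropathic symptoms, or temperature once its direction is changed.
- A reader might infer that the reference limb could be missing, since the article names only previous major amputation in the target limb. It refers to the registry for the detailed eligibility criteria, which are not at hand, so this cannot be claimed.
- Any single figure for the apparent harm would rest on one assumed shift. Only a range is defensible.

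**Conclusion.** The direction of the temperature component is an error in the outcome as stated, or at least an unexplained contradiction of the trial's rationale and of outcomes (a) and (d). As written, a warming effect counts against active treatment. On the treated limb alone, warming of 0.25 to 0.8 SD would show as about 10 to 29 points fewer patients improved; as a difference between independent limbs, about 7 to 21 points. These figures assume normal changes, no mean change on placebo and, for the between-limb version, no effect on the untreated leg.

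The contralateral reference in bilateral disease is a separate and lesser fault: it blurs the percentages in each group without reversing the comparison. Perimeter and neuropathic symptoms are scored in the expected direction. One component of one secondary outcome is affected; the primary safety outcome is not.

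**What to change.** Before unblinding:
1. Change the temperature criterion in outcome (f) to an increase. If a decrease is truly intended, say so and give the reason.
2. Make the treated limb's own change from baseline the main analysis of temperature and of perimeter. Compare it between arms as a continuous variable, as the Statistical analysis section already allows, with adjustment for the baseline value.
3. Keep the comparison with the contralateral limb as supportive, in patients with unilateral disease.

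The cost is a rewording of one outcome and its analysis. The schedule of procedures already has limb temperature and calf perimeter measured at the selection visit and at 3, 6 and 12 months, so no new data are needed. Making the change before unblinding matters, because a switch of direction after the results are known would look post hoc.

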## Background

Critical lower limb ischemia (CLI) is characterized by chronic pain at rest, ulcers or gangrene attributable to a proven occlusive arterial disease [1]. The evolution of CLI, in the context of a generalized atherosclerotic disease, implies high morbidity and mortality. CLI develops earlier and with greater intensity in patients with diabetes mellitus, with complications that may result in the amputation of the limb and even death [2, 3]. A public health goal of the standard of care is to decrease global cardiovascular risk through the control of risk factors by changes on lifestyle habits (quitting smoking, healthy diet, physical exercise) and pharmacological treatment (antiplatelet therapy, statins) [4]. However, there is insufficient evidence to show that this approach improves substantially the course of this disease [5]. Surgical or endovascular revascularization is often the treatment of choice, despite the fact that it is an invasive procedure that carries a high rate of complications. In addition, the health cost of this pathology is quite high. The treatment of the diabetic foot, and specifically critical limb ischemia, is the second most expensive complication in economic terms for the health system, just behind dialysis [6]. Efforts to prevent loss of the affected limb also include soft tissue debridement, minor amputations, and even skin grafts, all of which are costly procedures. In this context, given the high number of amputations that are still practiced annually worldwide, we are still in need of a cost-effective and easy-to-apply treatment [7]. Recently, research has shown that it is possible to improve tissue perfusion through therapeutic angiogenesis, making it one of the most promising strategies used to promote the proliferation of collateral vessels in ischemic tissues. In this sense, there are several methods to improve tissue perfusion, such as the administration of recombinant growth factors [8–11], or the constitutive expression of genes that encode for these factors through gene therapy [12]. Although both therapies have shown to promote angiogenesis in ischemic conditions in preclinical models [13], modest results were obtained when clinically applied [14–17]. In contrast, it has been shown both in animal models and in humans that cell therapy can induce therapeutic angiogenesis [18–20]. Cell-based therapies aiming to promote vascular regeneration gained interest with the discovery of a subpopulation of vasculogenic endothelial progenitor cells as reported by Asahara et al [17]. Human endothelial cell progenitors were isolated from peripheral blood by magnetic bead selection based on cell surface antigen expression. In animal models of ischemia, these cells have the ability to colonize the site of injury of ischemic tissue and secrete a number of vascular growth factors that can lead to clinically effective neovascularization [17]. It seems that these cells contribute to angiogenesis through the secretion of angiogenic cytokines and proteases such as matrix metalloproteases (MMPs), among others, helping the stability and growth of the endothelial and vascular network [21]. In 2002, the pioneering results of the TACT study (Therapeutic Angiogenesis using Cell Transplantation study) were published, consisting of a pilot uncontrolled safety study (*n* = 25) and a randomized controlled clinical trial to evaluate the use of mononuclear cells of bone marrow (BM) by intramuscular injection in 22 patients for treat peripheral arterial disease (PAD). Cell therapy with BM-derived mononuclear cells significantly improved ABI (difference 0.09 [95% CI 0.06–0.11]), transcutaneous oxygen pressure (pTcO2), (13 [9–17]), rest pain (− 0.85 [− 1.6 to − 0.12]) and pain-free walking time (1.2 [0.7–1.7]) in all treated patients [22]. Unfortunately, those with poorly controlled diabetes were excluded from the trial. As the prevalence of PAD increases in patients with type 2 diabetes mellitus (type 2 DM) it is logical to assume that this population group is a potential candidate for cell therapy [22]. Since then, several studies have been carried out in which the transplantation of the mononuclear fraction of BM or peripheral blood has been shown to improve the endothelial function in the territories in which they were administered [23] and to improve ischemic pain and the healing of ulcers [24]. In a phase I/II, open-label, non-comparative clinical trial, safety and feasibility of treatment with autologous mesenchymal stromal cells (MSC) derived from BM and administered intra-arterially in patients with type 2 DM and lower limb ischemia was studied. All of the participants (*n* = 20) showed an increase in leg vascularization demonstrated by angiography and 100% of the ulcers healed. During the first year of follow-up, 7 minor amputations were performed, but no patient suffered a major amputation [25]. Cañizo et al. reported the first case of a patient with CLI treated with peripheral blood CD133+ cells. There were no major amputations and after 17 months of follow-up, patients experienced symptomatic and functional improvement. The group also observed the appearance of blood flow in the posterior tibial artery that was absent before the procedure [26]. The search for the most appropriate cell type for this pathology remains a challenge today [27], but the use of MSC is gaining prominence. The fact that these cells have trophic, immunomodulatory, and anti-inflammatory properties and liposuction is an easy and minimally invasive technique places them as suitable candidates for clinical use. The study that we propose here focuses on the development and optimization of an advanced therapy medicinal product (ATMP) based on adipose tissue-derived MSC (Ad-MSC) to be administered intramuscularly to patients with type 2 DM and CLI within a multicenter randomized phase II clinical trial, favoring the translation of this cellular therapy to clinical practice. If proven safe and effective, an accessible, easy and minimally invasive treatment will be available for patients without any other option or that can even be associated with existing surgical treatments and improve their results.

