### Adverse events

An adverse event (AE), also referred to as an adverse experience, can be any unfavorable and unintended sign (i.e., an abnormal laboratory finding), symptom, or disease temporally associated with the use of a drug (or other investigational therapy) and does not imply any judgment about causality. An AE can arise with any use of the drug (i.e., off-label use, use in combination with another drug and with any route of administration, formulation, or dose, including an overdose). A suspected adverse reaction (SAR) means any AR for which there is a reasonable possibility that the drug caused the AE. An AE is considered “serious” if (SAE), in the view of either the principal investigator, if it results in any of the following outcomes: death of subject; event with risk to life, that is, there was an immediate risk of subject death at the time the reaction was observed; hospitalization or prolongation of hospitalization; persistent or significant disability/incapacity; congenital anomaly; or birth defect or any other significant medical condition, i.e., important AEs that do not pose an immediate risk to life and do not result in death or hospitalization but may endanger the subject or may require intervention to prevent one of the outcomes listed. A suspected adverse reaction is considered “unexpected” if it is not listed in the safety reference information for the IMP or is not listed at the specificity or severity that has been observed or is not consistent with previously available, known risk information.

Causality and severity assessment of any occurring AE will be performed by the principal investigator. AE will be registered from administration of IMP to end of study visit. Investigator will actively ask patients about AE occurrence in every study visit. Also, AE may be spontaneously reported by the patients. All of them will be appropriately registered in the patient medical records. Only AR and SAE will be registered in eCRF and reported according to legal requirements. For the purposes of this study, proportion of amputations in each study group is a secondary outcome and will be registered specifically, so notification as SAE will not be performed unless its clinical course is different of more severe than expected.

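### The amputation outcome is a change in a percentage for a once-only event, conflicts with the safety section, and has no rule for death before 12 months

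*Protocol article*

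**What the plan says.** All references are to the protocol article.

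- **Secondary outcome measures, item (g):** "Mean change in percentage of amputations in each group at the end of the study will be registered". No limb, amputation level or denominator is given.
- **Adverse events:** the same outcome is described as a proportion: "proportion of amputations in each study group is a secondary outcome and will be registered specifically". The sentence goes on to say that "notification as SAE will not be performed unless its clinical course is different of more severe than expected".
- **Recruitment of eligible participants:** patients with "previous major amputation in the target limb will be excluded from the trial".
- **Background:** minor amputation is listed among the measures taken to avoid losing the limb. In the earlier open-label study of 20 patients, "7 minor amputations were performed, but no patient suffered a major amputation". The same section says that the disease carries high mortality.
- **Seriousness and recording (Adverse events):** the criteria begin with "death of subject; event with risk to life" and include hospitalisation and lasting disability. "Only AR and SAE will be registered in eCRF and reported according to legal requirements".
- **Primary outcome measure:** treatment-related complications, compared between groups. The Adverse events section leaves causality to the principal investigator.
- **Statistical analysis:** the set called ITT is patients who consented and received product. The PP set is patients who complete 12 months. Qualitative outcomes are compared by chi-square or Fisher's exact test. Missing values are ignored below 5%, imputed up to 25%, and above that the variable is dropped. Death is not mentioned.

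**The concern.** Three things are unsettled for the event that gives the trial its acronym (no more amputations).

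First, the measure. A mean change suits a quantity measured twice in each patient. A first major amputation of the target limb either happens or does not, from a baseline of none.

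Second, what counts. The Background treats minor amputation as part of saving the limb and reports it apart from major amputation. A figure that does not state the level cannot tell a saved limb from a lost one.

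Third, death. A patient who dies with the limb intact can no longer be amputated. If mortality differs between arms, an amputation-only percentage at study end mixes the effect on the limb with the effect on survival. Neither analysis set resolves this.

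At stake is whether the amputation result can be interpreted at all. An arm with more deaths could look equal or better on it.

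**Working it through.** **1. Is there a plan figure to reproduce?** No. The article gives no amputation rate, death rate, effect size or power. The only arithmetic is 3 × 30 = 90, which agrees with the stated total.

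**2. What a change would mean.**
- *Major amputation of the target limb.* The baseline is 0 in every arm by exclusion, so change = proportion at 12 months − 0 = that proportion. The wording adds nothing and should be the proportion, as the Adverse events section has it.
- *Any amputation, either limb.* The criteria listed in the article do not exclude earlier minor or contralateral amputations, so the baseline need not be zero. A patient who enters with a minor amputation and then loses the limb is counted at both times and contributes no change.

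One reading is redundant and the other misses events. The text does not choose between them.

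**3. Effect of leaving death unhandled.** All counts are assumptions, with 30 per arm. Let A = patients amputated and D = patients who died without amputation. Amputated patients are assumed to complete follow-up.

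Formulas: amputated, all treated = A/30; amputated, deaths dropped = A/(30 − D); amputated or dead = (A + D)/30.

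| Assumed counts | Measure | Control | Active |
|---|---|---|---|
| Control A = 6, D = 3; active A = 6, D = 9 | All treated | 6/30 = 20% | 6/30 = 20% |
| | Deaths dropped | 6/27 = 22.2% | 6/21 = 28.6% |
| | Amputated or dead | 9/30 = 30% | 15/30 = 50% (Fisher p = 0.19) |
| Control A = 6, D = 2; active A = 4, D = 10 | All treated | 6/30 = 20% | 4/30 = 13.3% |
| | Deaths dropped | 6/28 = 21.4% | 4/20 = 20.0% |
| | Amputated or dead | 8/30 = 26.7% | 14/30 = 46.7% (Fisher p = 0.18) |

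In both cases the active arm is 20 points worse on amputation or death. The amputation-only figure shows no difference or an apparent benefit when all treated patients are counted. With deaths dropped it shows harm in the first case and near equality in the second. The choice of denominator therefore decides what is seen.

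**4. The missing-data rule does not settle it.** If deaths without amputation were treated as missing, each case has 12 such patients in two arms. With 0 to 10 more in the third arm the fraction is 12/90 = 13.3% to 22/90 = 24.4%. That lies in the band where values are imputed, so a limb status would be imputed for patients who had died. The article does not say whether this is intended.

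**5. What amputation-or-death could show at this size.** For assumed true rates of 30% and 50%, 30 per arm:
- two-sided 0.05: power about 35% (normal approximation) or 26% (exact Fisher);
- 0.05/4 for the four listed contrasts: about 17.5% or 12%;
- 80% power at 0.05 needs about 93 per arm.

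Precision in the second case: difference = 46.7% − 26.7% = 20 points; SE = √(0.267 × 0.733/30 + 0.467 × 0.533/30) = 0.122; 95% CI = 20 ± 1.96 × 12.2, about −4 to 44 points.

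**The case against.** A reader might infer that the plan lets excess mortality or limb loss go unseen. The text does not support that. Death is a seriousness criterion and is not exempted, so deaths enter the eCRF as SAEs. Amputations are recorded separately and reported by group, and the SAE waiver has its own exception. A crude excess of either would be visible at study end.

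Nor is the primary outcome closed to amputation. An amputation judged related to treatment is an adverse reaction. Adverse reactions go into the eCRF, and the primary outcome covers complications after the procedure. Unrelated amputations are left out because that outcome is limited to treatment-related events, not because of the waiver. The Abstract describes the primary outcome more broadly, as adverse events.

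Three further points stand. The article does not say that minor and major amputations are pooled; it is silent on level, and a condensed article may leave that to the full protocol. The zero-baseline argument covers only major amputation of the target limb. The direction of any distortion depends on an unstated denominator, and the illustrations assume large mortality differences that SAE listings would show.

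This narrows the point but does not remove it. Item (g) still contradicts the Adverse events section on the same outcome. A chi-square or Fisher test compares whatever percentages it is given and does not say how a patient who died should count.

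**Conclusion.** The point holds in limited form. As worded, (g) is not a workable measure and disagrees with the Adverse events section. Limb and level are open. Death before 12 months appears in no outcome and has no rule, and the PP set drops patients who die.

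The size cannot be estimated from the article. Under assumed counts, an amputation-only percentage can be equal (20% vs 20%) or apparently favourable (20% vs 13.3%) while amputation or death is 20 points worse. Whether that happens depends on a mortality difference between arms and on whether deaths stay in the denominator.

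On safety, the conclusion stops short of concealment. Amputations of expected course are not notified as SAEs, which weakens SAE-based detection during the trial. Those judged unrelated do not enter the primary comparison. Parts of the article were not available, so nothing is concluded about other safety monitoring.

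**What to change.** 1. Reconcile item (g) with the Adverse events section. Define (g) as the proportion of patients with major amputation of the target limb by 12 months, with all patients in the analysis set in the denominator.
2. Add amputation-free survival, with major target-limb amputation or death from any cause as the event. Give Kaplan-Meier estimates by arm and 12-month differences with 95% CIs.
3. Match the time origin to the analysis set. Randomisation is at the baseline visit (day −20 to −1), but the ITT set requires receipt of product. Counting from randomisation would credit treated patients with time in which they could not have failed. Count from treatment administration for the treated set, or from randomisation only if all randomised patients are analysed.
4. Tabulate major amputations, minor amputations and deaths separately by arm. Show all major target-limb amputations by arm beside the primary safety table, whether or not notified as SAEs.

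**Cost.** Mostly wording and tables. Dates of amputation and death must be captured in the eCRF; the article does not state that they are. The composite mixes limb loss with death, so its components must always be shown. With 30 per arm the intervals will be wide, so the result is an estimate and not a powered test.
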